## Introduction

### Background

There is a consensus from both cross-sectional and longitudinal research on the pattern of changes associated with aging, especially among older adults. With aging comes a natural decline in muscle mass and strength, leading to risks such as falls, fractures, disability, and a loss of independence [1]. Along with physical decline, research evidence has shown nearly a linear decline in cognitive function based on measures representing efficiency or effectiveness of information processing [2]. Research conducted in the United Kingdom and Malaysia has shown much poorer performance in theory of mind and working memory in the Malaysian older adult population compared to the other 3 groups (British young and older adults and Malaysian young adults). Many of these findings are moderated by educational levels, which suggests that interventions aimed at older adults need to be targeted accordingly [3]. According to Carstensen [4,5], the sense of future time, particularly the approach of endings such as the end of life, elicits cognitive, emotional, and motivational changes [4,5]; for example, aging is associated with a trend toward favoring positive over negative stimuli in cognitive processing [6]. This potentially introduces risks regarding how older adults make important decisions that have financial consequences in their daily lives; this is supported by evidence from research linking age-related changes in brain activity and physiology with financial decision-making [7,8].

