## Methods

### Trial Design

This quasi-randomized controlled trial has a longitudinal mixed-subject design for a total of 4 years (between-subject: intervention type; within-subject: repeated measures on various tasks and assessments). Participants will be quasi-randomly allocated to 1 of the 4 groups (cognitive stimulation, physical activity, combined cognitive stimulation and physical activity, and control) in a sequential cycle by experimenters to ensure balance in group sizes. Minor adjustments may be made for a small proportion of participants (anticipated to be fewer than 15% of the intervention sample) to accommodate logistical feasibility, such as availability during intervention sessions or access to required resources (eg, internet-enabled devices for online cognitive sessions). These adjustments will be applied only when necessary. Participants and experimenters will not be blinded to group assignment. Participants will be tested at baseline and every 6 months until the end of 4 years. Structural magnetic resonance imaging (MRI) will only be performed at baseline and at the end of the intervention period.

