### Exclusion Criteria

The exclusion criteria are (1) history of stroke, (2) diagnosis of a neurodegenerative disease (such as Alzheimer disease or Parkinson disease), (3) diagnosis of psychiatric disorders and/or being currently on psychiatric medications, (4) uncorrected auditory and/or visual impairments, (5) immobility or requirement for full-time caregiver assistance, (6) comprehension impediments or a Montreal Cognitive Assessment (MoCA) [29] score of less than 13.

Although the suggested cutoff score for the MoCA is 26, this might not be a true reflection of mild cognitive impairment in every country; hence, modifications to the cutoff score can be made according to the cultural and educational backgrounds of individuals in a particular country [30]. A systematic review of studies that used the MoCA in Southeast Asia reported that, in countries such as Malaysia, Singapore, China, and Taiwan, researchers used a cutoff ranging from 13 to 26 to take the educational background in these regions into account [31].

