### Baseline Measurements

The MoCA scores obtained by participants during their recruitment will serve as their baseline cognitive scores. In addition, cognitive behavioral measurements (2-back memory task [33], Wisconsin card sorting task [34,35], Tower of London task [36], and go/no-go task [37]), an electroencephalogram (EEG; resting state and during the go/no-go task), structural MRI, the everyday problem-solving task [38], and the Iowa gambling task [39] will be administered at baseline.

Participants will also answer a baseline questionnaire with regard to their demographics (gender, age, ethnicity, religion, spoken languages, marital status, occupation, educational level, savings, debts, assets, and social activities), health conditions (extracted questions from the Mini Nutritional Assessment [40] and Pittsburgh Sleep Quality Index [41] and voluntary disclosure of medical conditions), physical activity status (International Physical Activity Questionnaire) [42], mental health status (selected questions from the Center for Epidemiologic Studies Depression Scale [43] and State-Trait Anxiety Inventory [44]), Satisfaction With Life Scale [45], and life-course socioeconomic status (childhood, adulthood, and late adulthood). Participants may choose not to answer specific questions. In addition, saliva samples will be collected.

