### Statistical Methods

The primary analysis will be conducted using a repeated-measure linear mixed-effects model with time (baseline vs postintervention time point) as a within-subject factor and intervention type (cognitive stimulation vs physical activity vs combined vs control) as a between-subject factor. Participants will be included as a random effect to account for repeated measurements. Analyses will follow the intention-to-treat (ITT) principle, with baseline covariates such as age and sex included as fixed effects where appropriate.

Missing data will be handled using both ITT and per-protocol approaches. For participants with minimal missing data (<15%), analyses will primarily follow ITT principles without imputation, as this level of missingness is unlikely to bias the results. If missing data exceed this threshold, appropriate imputation methods, such as multiple imputation, will be applied. Sensitivity analyses will also be conducted to ensure robustness across both ITT and per-protocol analyses.

For exploratory purposes, paired 2-tailed *t* tests may be conducted to compare outcome values (before and after the intervention for each intervention phase, eg, telomere length), and one-way ANOVA may be used for simple between-group comparisons at a single time point. Results with a *P* value of less than .05 will be considered statistically significant, with appropriate attention to multiple testing for secondary analyses.

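### Age and sex entered only as main effects do not adjust the group-by-time contrast; the primary model should state covariate-by-time terms

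*Protocol article*

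**What the plan says.** Statistical Methods sets the primary analysis as a "repeated-measure linear mixed-effects model with time (baseline vs postintervention time point) as a within-subject factor", with the four intervention groups as the between-subject factor. The next sentence reads "Participants will be included as a random effect to account for repeated measurements". Covariates then enter "with baseline covariates such as age and sex included as fixed effects where appropriate". The section neither states nor excludes covariate-by-time terms or the baseline outcome as a covariate.

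Sample Size powers a 2 × 2 mixed-design interaction, so the effect the trial is built to test is group-by-time.

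Trial Design calls the allocation quasi-random. It runs "in a sequential cycle by experimenters to ensure balance in group sizes", without blinding, and logistical adjustments are anticipated for fewer than 15% of the intervention sample, for reasons such as session availability or access to a device.

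Baseline Measurements lists age and gender among the demographic items, as well as "marital status, occupation, educational level, savings, debts, assets, and social activities".

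**The concern.** Group-by-time compares within-person change between arms. A covariate that does not vary over time, entered only as a main effect, describes how high or low a person scores on average. It says nothing about how fast that person changes. If one arm is older and older people decline faster, the faster decline stays in the arm's estimated effect whether or not age is in the model.

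This matters more here than after concealed randomisation. Experimenters who are not blinded allocate in a predictable cycle and may then move some participants, so the arms could differ in characteristics that relate to rate of decline. A reader of the results would take the primary contrast to be adjusted for age and sex when, on the usual reading of the clause, it is not. The qualifier 'where appropriate' also leaves the choice of covariates open in an unblinded trial whose Results section says that analyses of intervention outcomes are already under way.

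**Working it through.** **1. The plan's own figures.** Inputs from Sample Size: 80 per group, partial eta squared 0.06, correlation at least 0.8, power 86.6%, attrition 20%. From Statistical Methods: alpha 0.05 (two-sided assumed).

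- f² = 0.06/0.94 = 0.0638. With noncentrality 0.0638 × 158 = 10.085 on F(1,158), power is 88.4%; with f = 0.25 and noncentrality 0.0625 × 160 = 10, it is 88.2%. Both lie within 2 points of 86.6%, which itself corresponds to partial eta squared of about 0.057. The figure is reproduced.
- 4 × 80 = 320, and 320/0.8 = 400, as stated.
- Implied design effect: 2 × √0.0638 = 0.505 SD of change. The SD of change at r = 0.8 is √(2 × 0.2) = 0.632 of the single-time SD, so the effect is 0.505 × 0.632 = 0.32 SD.

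**2. Algebra.** Take time t = 0 or 1, group g and baseline covariate x, with x as a main effect:

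y = a + b_g + c·t + d_g·t + γ·x + u + e

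For a participant seen twice, the change is

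y₁ − y₀ = c + d_g + (e₁ − e₀)

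The term γ·x cancels, as do the random intercept u and the level difference b_g. The estimate of d_g is the difference in mean change with or without x, and its standard error depends on the within-person residual variance, which x does not touch. If a term δ·x·t is added, the change becomes c + d_g + δ·x + (e₁ − e₀), and x now acts on the contrast. Leaving that term out biases d_g by δ times the between-arm difference in mean x.

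**3. Numerical check.** The model was fitted by REML with a random intercept to 60 simulated trials of 4 × 80. Assumptions: true effect 0.30; control arm 2 years older and 0.4 SD lower on education; change related to age (0.02 per year) and education (0.3 per SD). Expected unadjusted estimate: 0.30 + 2 × 0.02 + 0.4 × 0.3 = 0.46.

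| Covariate terms | Mean estimate (SE), complete data | Mean estimate (SE), about 20% missing follow-up |
|---|---|---|
| None | 0.459 (0.112) | 0.465 (0.127) |
| Age, sex main effects | 0.459 (0.112) | 0.465 (0.127) |
| Age, sex, education main effects | 0.459 (0.112) | 0.463 (0.126) |
| Age, sex, education, each also by time | 0.289 (0.102) | 0.303 (0.116) |

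With complete data, main effects moved no estimate (0.000000) and no standard error by more than 0.000003. With missing follow-up, age and sex moved the estimate by at most 0.008 (0.008/0.127 = 0.07 of a standard error) and the SE by at most 0.0003. Adding education raised these to 0.022 and 0.0007. The small shifts arise because participants with baseline only contribute some between-person information. Time interactions brought the mean close to the true 0.30 and, on complete data, cut the variance by 1 − (0.1020/0.1119)² = 17%. That gain reflects the assumed slopes.

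**4. Size of a possible bias.** Bias = covariate slope on change × imbalance. The document gives neither, so the age values below are assumptions.

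| Decline per year of age | Gap 0 years | Gap 1 year | Gap 2 years |
|---|---|---|---|
| 0.02 SD | 0 | 0.02 SD (6% of 0.32) | 0.04 SD (13%) |
| 0.04 SD | 0 | 0.04 SD (13%) | 0.08 SD (25%) |

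If age had an SD of 6 years (assumed), the standard error of the difference in mean age between two arms of 80 would be 6 × √(2/80) = 0.95. A 2-year gap would be 2/0.95 = 2.1 standard errors, unusual by chance alone.

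**The case against.** The strongest reply is that the clause does not say main effects only. Coming straight after the sentence on the random effect, 'fixed effects' may simply separate fixed from random terms, and a covariate-by-time term is also a fixed effect. Exact model terms are often left to an analysis plan, which is not shown. The premise stands: a reader might infer that the plan rules out time interactions, and it does not. But the wording is ordinarily read as main effects, and an analyst who follows that reading gets an adjustment with no effect on the tested contrast. That is more than a missing detail.

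A reader might also infer that not naming education is itself the error. The documents do not support this. The list is open. By the algebra above, education as one more main effect would equally do nothing. The Background remark "Many of these findings are moderated by educational levels" concerns earlier research on theory of mind and working memory, and the Exclusion Criteria remark that "modifications to the cutoff score can be made according to the cultural and educational backgrounds of individuals" concerns score level, not rate of decline. Education belongs in the remedy because it is collected and plausibly prognostic.

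Nor is the contrast left with no protection: stable level differences drop out by design. Structural MRI has its own longitudinal linear models adjusting for age, sex and intracranial volume, and EEG its own 6-monthly mixed models with covariates; this point does not extend to those. Finally, the 0.08 SD is an illustration and not an estimate for this trial. Trial Design does not link the logistical adjustments to age.

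**Conclusion.** The concern holds in this form: read as main effects, the stated covariate adjustment leaves the group-by-time estimate and its standard error unchanged for participants with both time points, and practically unchanged at the planned 20% attrition. It therefore neither corrects imbalance in rate of change nor adds precision. The complete-data result is algebra and needs no assumption about imbalance or slopes; it rests on a random-intercept model with two time points and on the main-effects reading. Whether any bias exists, and how large it is, depends on figures the document does not give. The change is worth making because allocation is quasi-random and unblinded and the better specification costs almost nothing.

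**What to change.** In Statistical Methods, replace the covariate clause with a statement along these lines: *The primary model will contain intervention group, time and their interaction, with age, sex and educational level each entered as a main effect and in interaction with time.* Delete 'where appropriate', so that inclusion is not decided after unblinded data have been seen. Because analyses are reported as under way, date the change and say which outcomes had been analysed by then.

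A model of the postintervention score on the baseline score and the same covariates could serve as a sensitivity analysis. It is a different model, not an equivalent one: at r = 0.8 its residual variance is 1 − 0.8² = 0.36 against 2 × (1 − 0.8) = 0.40 for change, and with non-random allocation and baseline differences the two can give different estimates.

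The cost is text and a few degrees of freedom. All three covariates are already collected. The categories of educational level need to be fixed, with a rule for missing values, since Baseline Measurements lets participants skip questions.

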### Sample Size

Simulation-based power analysis was performed using the *superpower* R package [46] in RStudio (version 2023.06.1; Posit PBC). This analysis determined that a sample size of 80 participants per intervention group would be sufficient to detect a medium effect size (η^2^_p_=0.06) in a 2 × 2 mixed-design interaction with 86.6% power. The 2 × 2 design was chosen as a comparison of pre- and postintervention measures between an intervention and control group, providing a basic assessment of whether a specific intervention is effective. This assumes a correlation of at least 0.8 between repeated measures. We calculated that a sample of 400 would be necessary to reach our goals, given that we expect an attrition rate of 20% (80/400 participants) between the pre- and postintervention phases for several reasons (ie, death, decline in health, and dropouts in training sessions).

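### The 15% missing-data rule rests on the amount missing rather than the reason, has no stated denominator, and can treat the same missing year-4 value in opposite ways

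*Protocol article*

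**What the plan says.** In the Protocol article, Statistical Methods, the primary analysis is a linear mixed-effects model under intention to treat (ITT). Participant is a random effect, there are four groups, and time has two levels: baseline and after the intervention. The missing-data paragraph opens with "Missing data will be handled using both ITT and per-protocol approaches". It continues that, for participants with less than 15% missing, "analyses will primarily follow ITT principles without imputation, as this level of missingness is unlikely to bias the results". The other branch is "If missing data exceed this threshold, appropriate imputation methods, such as multiple imputation, will be applied". The sensitivity analyses it names look at robustness across ITT and per-protocol.

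Under Sample Size, "we expect an attrition rate of 20% (80/400 participants) between the pre- and postintervention phases", and the reasons given are "ie, death, decline in health, and dropouts in training sessions".

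Four other sections bear on this:
- **Trial Design** schedules testing at baseline and every 6 months for 4 years, without blinding.
- **Interim Measurements** repeats the MoCA, cognitive tasks, EEG and saliva collection at each six-monthly visit.
- **Control Group** states that controls attend no intervention sessions.
- **EEG Measurement** already describes mixed-effects modelling at 6-month intervals.

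**The concern.** The rule treats a quantity of missing data as evidence of safety. A small share can bias a comparison if those lost differ from those kept and the loss differs between arms. A larger share may do no harm if loss works the same way in every arm. The article's own list of expected causes points to the harmful case. Death and declining health are plausibly related to an outcome defined as aging-related decline, and dropout from training can occur only where there is training. If the people declining fastest leave the active arms more often than the control arm, those who remain make the intervention look better than it is. Other patterns could hide a benefit.

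The rule is also ambiguous. The first branch is worded per participant, the second has no unit, and the percentage has no denominator. Because allocation is open, leaving that choice until outcome data are being analysed is undesirable.

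**Working it through.** **1. The plan's own figures.** Four groups of 80 give 320 completers, and 320 / (1 − 0.20) = 400, as stated. For power, partial η² = 0.06 gives f² = 0.06/0.94 = 0.0638. With 1 and 158 degrees of freedom, λ = 0.0638 × 158 = 10.09, and power is 88.4% at α = 0.05. The stated 86.6% came from simulation, so this is close enough. With correlation 0.8, the variance of change is 2 × (1 − 0.8) = 0.4 in baseline-SD units. The design effect is therefore √10.09 × √0.4 × √(2/80) = 0.318 baseline SD.

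**2. Applying the 15% rule.** There are 8 six-monthly visits plus baseline, so 9 in all.

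| Case | Denominator | Share missing | Branch |
|---|---|---|---|
| Year 4 only | all 9 visits | 1/9 = 11.1% | no imputation |
| Year 4 only | 8 follow-up visits | 1/8 = 12.5% | no imputation |
| Year 4 only | 2 modelled time points | 1/2 = 50% | imputation |
| Last two visits | all 9 visits | 2/9 = 22.2% | imputation |
| Last two visits | 8 follow-up visits | 2/8 = 25.0% | imputation |
| Whole trial, expected loss | 400 participants | 80/400 = 20% | imputation |

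One missing year-4 value thus falls in either branch depending on an unstated denominator. Counted by visit, two participants who both lack the year-4 value are handled differently because one of them also missed month 42.

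**3. Amount versus mechanism (assumed values, not from the documents).** If a proportion p of an arm is lost and those lost decline g SD more than completers, the completers' mean change is too favourable by p × g. The bias in the arm difference is (p_active − p_control) × g.
- Take 17% loss in each active arm and 5% in control. Overall loss is (3 × 17 + 5)/4 = 14%, under the threshold.
- Bias = (0.17 − 0.05) × 0.5 = 0.06 SD, and × 1.0 = 0.12 SD.
- Relative to 0.318 SD, this is 0.06/0.318 = 19% to 0.12/0.318 = 38%.
- With equal p and equal g in every arm, the bias is 0 at any percentage.

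**4. Does baseline adjustment remove it?** This was simulated with 200,000 per arm, correlation 0.8 and a true effect of 0.318 SD. The estimate regresses the final value on baseline among those observed.

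| Loss | Same mechanism in both arms | Worst decliners lost in active arm only, random loss in control |
|---|---|---|
| 10% | 0.321 | 0.405 |
| 14% | 0.317 | 0.431 |
| 20% | 0.316 | 0.456 |

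The right-hand column is a deliberately severe case: half of the worst-declining tail is lost from the active arm. The contrast between columns shows that mechanism governs the bias. At 10% loss the excess is already 0.405 − 0.318 = 0.087 SD, while at 20% with a common mechanism it is negligible.

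**The case against.** The case for the plan is substantial, and most of it stands.

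- **A reader might infer that data under 15% missing get no handling.** The text does not say so. It rules out imputation inside a mixed model. Fitted by likelihood, that model keeps participants who have only a baseline value and is valid if data are missing at random. The limit is that, with two time points, missingness can be explained only by baseline and covariates. Six-monthly values observed before dropout are not used.
- **A reader might infer that the expected 20% contradicts the rule.** It does not. At trial level 20% exceeds 15% and leads to the multiple-imputation branch, which is the rule operating.
- **A reader might state as fact that a missing year-4 value goes unimputed.** That holds by visit count and reverses if the two modelled time points are counted.
- **A reader might take a 20% active, 8% control split as a case under the threshold.** It averages 14% for one active arm against control. Over three active arms and control it is (3 × 20 + 8)/4 = 17%.
- **Per-protocol is already secondary.** ITT leads throughout, so the objection to calling per-protocol a missing-data approach is one of wording.
- **Sensitivity detail may sit in an analysis plan that is not shown.** The absence of a delta-adjusted analysis from an article is therefore not itself a fault.

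What the defence does not answer is that the article makes a positive statement, and the statement is wrong. A full analysis plan would have to contradict it, not merely add detail. The named check, ITT against per-protocol, changes who is analysed. It does not test whether unobserved values differ from observed ones.

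**Conclusion.** The point holds at moderate severity. The article justifies omitting imputation by the amount missing, when the mechanism and its balance across arms decide the matter, and its own expected reasons for loss make an informative, arm-dependent mechanism plausible. The threshold has no denominator, so the same missing primary value can be imputed or not. The two-time-point model sets aside interim data that would make the missing-at-random assumption more credible.

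The 0.06 to 0.12 SD figure is an illustration. It assumes a 12-point gap in loss between active and control arms, extra decline of 0.5 to 1.0 SD in those lost, and a complete-case comparison that gives no credit to baseline or covariates. The documents supply none of these values and do not show that such bias will occur. With the same loss mechanism in all arms it would be about zero.

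**What to change.** 1. Delete the 15% threshold and the clause claiming that such an amount is harmless.
2. For outcomes measured every 6 months (MoCA, cognitive tasks, EEG, saliva), fit the likelihood-based mixed model to all observed visits, whatever the percentage missing, with the year-4 group contrast as the estimate. Treat visit as categorical and choose a covariance structure suited to nine visits. The EEG section already describes six-monthly mixed modelling, so this aligns the two sections. Structural MRI has only two scans, so step 2 adds nothing there and step 3 carries the weight.
3. Add a delta-adjusted sensitivity analysis in which the assumed shift for missing values varies by arm, and report deaths separately by arm.
4. Describe per-protocol as a supplementary analysis set, not as a way of handling missing data.

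The cost is a revised paragraph and one further sensitivity analysis, with no new data or visits. Settle it before the intervention outcome publications anticipated from 2026.

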The overarching aims of this project are to assess cognitive function across a broad range of measures, contextualize these measures within additional demographic and lifestyle data, implement and validate evidence-based interventions derived from theories of cognitive decline that incorporate both physical and cognitive activities, and assess the effectiveness of these interventions in modulating the trajectory of age-related cognitive decline in a socioeconomically and ethnically diverse Asian sample. The main objectives and specific objectives are summarized in the following sections. In this paper, we propose the comparison of 3 long-term interventions (cognitive stimulation, physical activity, and combined cognitive stimulation and physical activity) against a passive control condition. These interventions will be administered over an extended period (4 years). We hypothesize that these interventions can, over 4 years, significantly slow down the normal rate of aging-related decline in cognitive function and brain structure and function, and change the expression of aging-related salivary biomarkers. We predict that cognitive stimulation and physical activity will lead to a significant reduction in aging-related decline as compared to the nonintervention control. In addition, we predict that the combined cognitive stimulation and physical activity intervention will yield the most significant reduction in aging-related decline as compared to cognitive stimulation alone, physical activity alone, and the control condition. The overall structure of the program is shown in Figure 1. These 5 separate projects are interrelated not only because they involve the same participants but, more importantly, because they all aim to delay aging-related decline. Age-related decline is manifested in individuals’ cognitive and behavioral functions, neural markers of cognition, decision-making, and biological markers. The effectiveness of the cognitive and/or physical interventions will be measured (projects 1, 2, 3, and 5), and the economic impact of such long-term interventions in a cost-benefit analysis will also be evaluated (project 4).

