## Results

From the perspective of psychology, primary outcomes will be the changes in cognitive scores (MoCA), cognitive behavioral measurements, everyday problem-solving, and Iowa gambling tasks. From the perspective of neuroscience, primary outcomes will be the changes in EEG and MRI. From the perspective of economics, the primary outcome will be the cost-benefit analysis of the intervention. From the perspective of biology, primary outcomes will be the changes in salivary biomarkers (lactoferrin, CRP, and telomere length).

The study grant was awarded in August 2019. Participant recruitment was delayed due to the COVID-19 pandemic, as the target population comprised healthy older adults who were particularly vulnerable during periods of movement restrictions and heightened infection risk. Recruitment commenced in May 2022 and was completed in July 2023. A total of 400 healthy older adults were successfully enrolled. The intervention phase began in 2023 and is currently ongoing, with participants undergoing intervention activities and follow-up assessments at 6-month intervals throughout the study period. At the time of manuscript submission, follow-up data collection and data analysis are ongoing. Baseline characteristics and cross-sectional findings from the cohort have been reported separately, while analyses of intervention-related outcomes are currently underway. The first intervention outcome publications are anticipated from 2026 onwards as follow-up assessments are completed, and additional longitudinal data are available for analysis.

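### All tested outcomes are primary and unranked, yet multiplicity control at P<.05 is promised only for secondary analyses, so the false-positive rate across the primary outcomes is well above 5% on every reading

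*Protocol article*

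**What the plan says.** **Outcomes.** The Results section assigns primary outcomes by discipline.

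- Psychology: change in MoCA, the cognitive behavioral measurements, everyday problem-solving and the Iowa gambling task. Baseline Measurements lists four cognitive behavioral tasks: 2-back, Wisconsin card sorting, Tower of London and go/no-go.
- Neuroscience: EEG and MRI.
- Biology: "primary outcomes will be the changes in salivary biomarkers (lactoferrin, CRP, and telomere length").
- Economics: the cost-benefit analysis, for which no hypothesis test is described.

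No outcome is ranked above another and none is called secondary.

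**Contrasts.** The Background predicts that each single modality will beat control. It also predicts that "the combined cognitive stimulation and physical activity intervention will yield the most significant reduction in aging-related decline as compared to cognitive stimulation alone", than physical activity alone, and than control. That makes five contrasts.

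**Test level.** Statistical Methods specifies a linear mixed model with time and a four-level intervention factor, and then this rule: results with P below .05 "will be considered statistically significant, with appropriate attention to multiple testing for secondary analyses". It says nothing on multiple testing for the primary outcomes.

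**Power.** Sample Size states that 80 per group detects a partial eta squared of 0.06 "in a 2 × 2 mixed-design interaction with 86.6% power". It describes this as one intervention group against control, before versus after.

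**The concern.** The article does more than stay silent on multiplicity. It fixes a threshold and says where multiple testing will receive attention, and that place is a class of analyses to which it assigns no outcome. Followed as written, each of a dozen unranked primary outcomes can be declared positive at .05, possibly on several arm contrasts.

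The main objectives are framed broadly: whether the interventions slow aging-related decline. If any one of many primary tests can be offered in support, the nominal 5% no longer describes the risk of a false claim. The stated power likewise describes one comparison on one outcome, not the set of comparisons that the hypotheses call for.

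**Working it through.** **1. The plan's own power figure.** Inputs from Sample Size: 80 per group (160 per contrast), partial eta squared 0.06, one 2 × 2 interaction. Alpha is not stated there, so .05 is assumed.

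- f² = 0.06/0.94 = 0.0638.
- Noncentrality = f² × error df = 0.0638 × 158 = 10.09. Power of F(1,158) at .05 is 88.4%, within 2 points of the stated 86.6%.
- Solving backwards, 86.6% corresponds to noncentrality 9.53.
- Attrition: 320/0.80 = 400, as stated.

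The figure is therefore sound for one contrast on one outcome at an unadjusted .05.

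**2. Number of primary outcomes.** Psychology 1 + 4 + 1 + 1 = 7, neuroscience 2, biology 3, total 12. Everyday problem-solving and the Iowa gambling task are listed at baseline but not under Interim Measurements or End of Intervention Period. If they are not remeasured, 10 remain. EEG is counted once, although the EEG section describes resting-state recordings as well as event-related amplitudes and latencies.

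**3. One omnibus group-by-time test per outcome, no true effects.** For independent outcomes, the chance of at least one P<.05 is 1 − 0.95^m.

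- m = 12: 1 − 0.95^12 = 46.0%
- m = 10: 1 − 0.95^10 = 40.1%

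**4. Three active-versus-control contrasts per outcome, ungated.** The contrasts share the control arm, so on one outcome the chance of at least one P<.05 is about 12.5% (simulated), not 1 − 0.95³ = 14.3%. For independent outcomes:

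- m = 12: 1 − 0.875^12 = 79.9%
- m = 10: 1 − 0.875^10 = 73.7%

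**5. Correlated outcomes.** The article gives no between-outcome correlation, so a range is assumed. Simulation (100,000 trials, four equal arms, equicorrelated outcomes, two-sided tests at .05):

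| Outcomes | Correlation | Omnibus only | Three contrasts |
|---|---|---|---|
| 12 | 0 | 46% | 80% |
| 12 | 0.5 | 33% | 63% |
| 12 | 0.8 | 19% | 41% |
| 10 | 0 | 40% | 74% |
| 10 | 0.5 | 30% | 59% |
| 10 | 0.8 | 18% | 39% |

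With all five predicted contrasts ungated on 12 outcomes, the rate is about 91% at correlation 0 and 76% at 0.5.

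**6. Each project as its own family, independent omnibus tests.**

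- Psychology (7): 1 − 0.95^7 = 30.2%
- Neuroscience (2): 1 − 0.95² = 9.8%
- Biology (3): 1 − 0.95³ = 14.3%

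**7. Power at an adjusted level.** Starting from the stated 86.6% (noncentrality 9.53, 80 per arm):

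- .05/3: 74.7%, about 75%
- Dunnett for three contrasts (critical value about 2.37): about 76%
- .05/12, if 12 primary outcomes share one Bonferroni split: 57.2%

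**The case against.** **Omnibus reading.** The only specified primary analysis is a single mixed model with a four-level factor, whose natural test is one omnibus interaction. A reader might infer from the contrast-based figures that a false-positive primary claim is more likely than not. The documents do not support that as a fact. It needs ungated contrasts, one pooled family, a global null and a between-outcome correlation that is not given. On the omnibus reading, 12 tests stay below one half.

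**Separate projects.** The article describes five interrelated projects and assigns outcomes by discipline, so pooling telomere length with MoCA is a choice rather than a requirement. This stands, and the per-project rates are the relevant ones if no overall claim is made. They still exceed 5%.

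**Left to the analysis plan.** A condensed article may leave the procedure to a fuller document. That would answer a complaint about missing detail. It does not answer a stated rule whose scope leaves out the primary outcomes.

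**Power.** A reader might take 86.6% to be a miscalculation. It is not: the article openly says that it concerns one 2 × 2 comparison, and the figure is approximately reproduced. This is a limit of scope and not a separate error.

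**MoCA as the obvious sole primary.** The article criticises culturally biased psychometric tools, so it does not point to MoCA as the one confirmatory outcome. Choosing any single outcome now also risks data-driven selection, because outcome analyses are underway and group assignment is not blinded.

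**Conclusion.** The concern holds. The article names 12 (possibly 10) unranked primary outcomes, fixes P<.05, and confines attention to multiplicity to secondary analyses that it never identifies. If there are no true effects, the chance of at least one false-positive primary result is about 40% to 46% with one omnibus test per independent outcome (30% to 33% at correlation 0.5). It is about 74% to 80% with three ungated contrasts (59% to 63% at correlation 0.5). Within single projects it is about 10% to 30% for independent omnibus tests. Even one outcome with three unadjusted contrasts gives about 12.5%.

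The exact size depends on the between-outcome correlation, on whether contrasts are gated, and on how families are drawn, none of which the article states. The direction does not depend on these: every reading examined is well above 5%.

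**What to change.** 1. In Statistical Methods, extend error control to the primary outcomes. Use Dunnett or Holm across the three active-versus-control contrasts, and test combined-versus-single only after combined-versus-control succeeds. Apply Holm across the primary outcomes, at least within each project, and across projects if one overall claim of effectiveness will be made.
2. Alternatively, the sponsor may designate one confirmatory outcome and make the rest secondary, with the arm contrasts still adjusted.
3. Say whether everyday problem-solving and the Iowa gambling task are remeasured, so that the primary set is defined.
4. Record the date of the decision and what intervention data had been seen by then, since the Results section says that outcome analyses are underway.
5. In Sample Size, state that 86.6% applies to one outcome and one intervention-versus-control contrast, and give the alpha used. Add the power at the adjusted level: about 75% at .05/3 or 76% with Dunnett, with 80 per arm, and lower if several primary outcomes are kept.

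Cost: changes to the statistical text and a matching registry update. The stated power becomes less favourable. No extra participants are needed.
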